#### Implementation of the MAKS therapy in the DeTaMAKS project

The day-care centres in the intervention group committed themselves to carrying out the therapy in accordance with the manual every morning from Monday to Friday for 6 months. On each day of the therapy, all study participants attending the day-care centre on that day take part in the MAKS therapy. This results in average “doses of therapy” of one to five therapy days per week. The MAKS therapy is carried out by no less than two trained therapists. At least one of the two therapists is a qualified healthcare professional (geriatric nurse, nurse, or occupational therapist). The one-day training event for the staff of the day-care centres and the material used in the therapy were given to the day-care centres in the intervention group at baseline and will be given to the centres in the control group 6 months later. Study headquarters’ staff members are available to answer questions by phone or by e-mail on all weekdays.

The project does not exert any influence on the usual services of any of the 34 day-care centres, the pharmacotherapy of the study participants, or the frequency of attendance. Day-care users were free to choose their day-care centre and were free to decide whether to participate in the MAKS therapy. However, all changes in the frequency of attendance of the day-care centre are documented for all study participants.

A precursor to the intervention was implemented in nursing homes in a randomised-controlled trial [15] to record serious adverse events (falls resulting in injury, other types of serious injury and deaths), which did not increase over a period of 12 months. This is why we forwent the recording of serious adverse events (except death) and why no stopping guidelines were necessary. For this reason, we expect that the benefits of the MAKS therapy will far outweigh any possible harm. Also, because the intervention was implemented within the care of the day-care centres, participants did not need additional accident insurance.

#### Brief telephone intervention for informal caregivers

In addition to the MAKS therapy provided by the day-care centres, all caregivers in the intervention group receive three brief outreach telephone interventions. The task of the counsellors is to support the caregivers through three manualised phone calls, each lasting roughly 1 h. The goal is to work with the caregivers to develop strategies for self-management, to reduce the stress involved in providing home care, and to deal with challenging behaviours in order to “empower” the caregivers by improving their skills. The intervention includes tried and tested procedures from stress psychology, adjusted to fit the informal caregivers’ situations. Specifically, elements of the following procedures are employed: stress inoculation training as described by Meichenbaum [29], time structuring for the day, selection and prioritisation of goals, and development of positive activities. The procedure follows the self-management approach [30], that is, the aim is to enable the caregivers to use the strategies they have learned as fast as possible and to apply them in a beneficial manner.

“Challenging behaviours”, which occur in dementia in particular, are frequently experienced as especially stressful by caregivers. The intervention therefore includes information on the reasons for behaviour that is outside of the norm and the teaching of strategies that can be applied to reduce the occurrence of challenging behaviours, especially including references to the established Need-Driven Behaviour model to understand challenging behaviour [31, 32]. The counsellor’s basic attitude is client-centred [33] and solution-oriented.

The phone calls are made at the beginning of the 6-month intervention phase, after about 2 months, and towards the end of the intervention phase. The intervention is carried out by two counsellors with training in psychotherapy who were given special training beforehand and regular supervision. The first phone call begins by determining the specific stress triggers and the behaviours that the caregiver identifies as challenging, followed by an explanation of some initial possible coping modes and information about the challenging behaviours the caregiver has experienced. The telephone counsellors help the informal caregivers develop concrete changes in their own behaviour. When necessary, the counsellors suggest that the caregiver might wish to take advantage of support services in their area. In the second phone call, the behaviour changes proposed in the first phone call and their effects are discussed. The third phone call serves as a booster session and is made towards the end of the 6-month intervention phase. Jointly developed “homework” tasks are intended to support learning and to help caregivers work on their issues during the periods between the phone calls.

### Measures

The measures employed at the different measurement occasions are shown in Table 5.

**Table 5 Tab5:**
[figure not shown]
Timeline of measurements

*Abbreviations*: *BIZA-D* Berlin Inventory of caregivers’ burden with dementia patients, *BSFC-s* Burden Scale for Family Caregivers short, *CATI* computer assisted telephone interview, *CG* informal caregiver, *CRF* case report form, *DCC* day-care centre, *EQ-5D-5L* EuroQol five dimensions questionnaire, *ETAM* Erlangen test of activities of daily living in persons with mild dementia or mild cognitive impairment, *FIMA* Questionnaire for the use of medical and non-medical services in old age, *IG* intervention group, *MMSE* Mini-Mental State Examination, *MoCA* Montreal Cognitive Assessment, *NOSGER* Nurses’ Observation Scale for Geriatric Patients, *NPI-Q* Neuropsychiatric Inventory-Questionnaire, *PCI* person with cognitive impairment, *RUD* Resource Utilization in Dementia, *WHO-5* Well-Being Index

#### Primary outcome measures – People with cognitive impairment

Erlangen Test of Activities of Daily Living in Persons with Mild Dementia or Mild Cognitive Impairment (ETAM) [34]. The ETAM is a performance test for the assessment of the ability to perform ADL in people with mild dementia or mild cognitive impairment. It takes 19-35 *min* and consists of six items representing the five chapters of the domain “Activities and Participation” of the International Classification of Functioning, Disability, and Health (ICF). The score ranges from 0 to 30 points, with higher values showing better abilities to perform ADL. The ETAM meets the criteria for a well-constructed test [34].

*Mini-Mental State Examination (MMSE)* [35]. The MMSE is the most frequently employed screening test for dementia [36]. It measures five areas of cognitive functioning: orientation, registration, attention and calculation, recall, and language. The score ranges from 0 to 30 points, with higher scores representing better cognitive performance. Values above 23 points are interpreted as “not demented”. Scores between 0 and 23 are indicative of a dementia syndrome, more specifically, 18-23 points as “mild dementia”, 10-17 as “moderate dementia”, and 0-9 points as severe dementia [23].

#### Primary outcome measures – Caregivers

*Burden Scale for Family Caregivers short (BSFC-s)* [37]. The BSFC-s is used to assess the subjective burden of informal caregivers. The ten items of the short version are rated on a scale ranging from 0 (strongly disagree) to 3 (strongly agree). The total score ranges from 0 to 30 points, with higher values indicating a greater burden.

*WHO-5 Well-Being Index (WHO-5)* [38, 39]. The WHO-5 is employed to assess well-being during the last 14 days. Five positively poled statements are rated on a 6-point scale ranging from 0 (At no time) to 5 (All of the time). The score ranges from 0 to 25 points, with higher values indicating greater well-being.

#### Secondary outcome measures – People with cognitive impairment

*EuroQol five dimensions questionnaire (EQ-5D-5L)* [40]. The EQ-5D-5L assesses health-related quality of life. It consists of the five items mobility, self-care, usual activities, pain/discomfort, and anxiety/depression. Each item is rated on a five-point scale.

*Neuropsychiatric Inventory Questionnaire (NPI-Q)* [41]. The NPI-Q is an observer rating scale for the evaluation of neuropsychiatric symptoms by the informal caregiver covering the 12 symptom areas delusions, hallucinations, agitation/aggression, depression/dysphoria, anxiety, elation/euphoria, apathy/indifference, disinhibition, irritability/lability, motor disturbance, night time behaviours, appetite/eating. Each symptom is tested with a screening question (present yes/no). If the response to a screening question is “yes”, specific aspects (domains) are explored further. In this study, only the screening questions were asked.

*Nurses’ Observation Scale for Geriatric Patients (NOSGER)* [42]*.* The NOSGER is an observer rating scale for assessing general abnormalities in the elderly. It consists of six subscales (mood, disturbing behaviour, social behaviour, memory, ADL, and instrumental activities of daily living (IADL)). Each subscale contains 5 items. Each item is rated on a 5-point scale ranging from 1 (always) to 5 (never). The number of points that could be scored for each subscale ranges from 5 to 25, with higher values indicating greater impairment. In this study, we used the “social behaviour” subscale.

#### Secondary outcome measures – Caregivers

*EQ-5D-5L* [40]*.* The EQ-5D-5L is used to evaluate the caregivers’ health-related quality of life.

*Berlin Inventory of caregivers’ burden with dementia patients (Berliner Inventar zur Angehörigenbelastung – Demenz, BIZA-D)* [43]. The BIZA-D is employed to assess psychosocial impairment in caregivers arising from caregiving. The measure contains 88 items divided into 20 subscales. Only the “benefits” subscale is used in this study. This subscale contains 5 items that are rated on a five-point scale. The score ranges from 0 to 20 points, with higher values indicating more “benefits”.

#### Other measures

*Montreal Cognitive Assessment (MoCA)* [25]. The MoCA is a measure that is used to screen for MCI. It consists of more difficult items than the MMSE and is thus able to better detect MCI [24, 26, 44, 45]. The score ranges from 0 to 30 points, with higher scores indicating better cognitive performance. A score of 22 or less is indicative of cognitive impairment [26].

*Resource Utilization in Dementia (RUD) questionnaire* [46]*.* The RUD is the measure that is used the most around the world to collect data on the use of resources in dementia, enabling comparisons of costs of care across countries with different health care provisions. It evaluates formal and informal care, specifically the use of resources by both the people requiring care and their informal caregivers. The part of the questionnaire that refers to formal care was adjusted to fit the German healthcare system.

*Questionnaire for the use of medical and non-medical services in old age (Fragebogen zur Inanspruchnahme medizinischer und nicht-medizinischer Versorgungsleistungen im Alter, FIMA)* [47]*.* This questionnaire is used to collect data on the use of healthcare resources by elderly people. It assesses the quantities and time periods for the services that are used. In this study, we used the subscale “nursing and household care”, which asks about formal care in detail.

*Users’ personal and medical histories.* The following data from the users’ histories were recorded in standardised form by the staff of the day-care centres at the start of the study (baseline): sociodemographic data (age, sex), information about their care situations (date of first visit to the day-care centre and frequency of attendance, level of care, use of an outpatient homecare service), and medical data (diagnoses, medications). Caregivers were asked to provide information on family status, level of education, and the duration of the care situation for the user and for themselves. In order to be able to establish changes in the caregivers’ employment, living, and care situations, this information was recorded at each measurement occasion.

*Changes in the day-care centre situation (monthly)*. During the 6-month intervention phase, we kept track of the presence of the study participants. Specifically, we recorded periods of and reasons for extended absences (longer than 1 week), changes in the level of care, and whether the participants left the day-care centre (terminated the contract, moved to a nursing home, died) or the project (withdrew consent). These data were tracked daily and reported monthly.

*Evaluation of the MAKS therapy.* The MAKS therapists in the day-care centres in the intervention group documented the attendance of the study participants and any deviations from the manualised procedure on each day of therapy of the 6-month intervention period in order to monitor the intensity and quality of the MAKS therapy. After the end of the 6-month intervention period, the therapists at the day-care centres attended by the intervention group participants were also asked to submit their subjective assessments of the 3 most suitable and 3 least suitable tasks in each MAKS component. In addition, from the follow-up survey conducted after 6 months and onwards, the informal caregivers in both arms of the study were asked to rate potential changes in the care recipients’ alertness/activity, initiation of contact/talkativeness, physical mobility, mood, and thinking/memorising capacities on a 3-point scale (improved/remained the same/worse). They were also asked about the occurrence of three types of severe adverse events (falls resulting in injury, other injuries requiring medical treatment, and other serious adverse events).

In order to obtain information on the sustainability of the MAKS therapy 12 and 24 months after baseline, the day-care centres are asked how they are carrying out the MAKS treatment after the end of the 6-month intervention phase.

*Evaluation of the brief telephone intervention for informal caregivers.* After the end of the 6-month intervention phase, the caregivers in the intervention group were asked to evaluate the brief telephone intervention. The questionnaire contained 4 questions that pertained to satisfaction with the intervention (example: “I learned from the counselling how I can pay better attention to my own needs”) that were rated on a 3-point scale (“I totally agree”, “partly yes, partly no”, “I don’t agree at all”). They were also asked about qualitative aspects (“What did you like?”, “What did you dislike?”).

### Data collection

Data collection for the primary outcome variables pertaining to the people with cognitive impairment was conducted at the day-care centres by staff who were trained by the study headquarters staff. Data are collected at the beginning of the study, after the end of the 6-month intervention period, and after 12 months. To reduce the risk of investigator bias, the testers are not involved in the care of the day-care centre users.

The CATIs are administered to the caregivers by trained interviewers at the beginning of the study and after 6, 12, and 24 months in order to collect data on variables related to the caregivers’ situations (self-rating), the day-care users’ situations (observer rating), and the care situation. The procedure of CATI is described in detail by Holle et al. [48]. A short form of the questionnaire is sent to the caregivers to prepare them for the interview. All the other data mentioned in the previous section are collected by trained day-care centre staff in a standardised, written form.

The final data set consists of data collected at the day-care centres and via CATIs. The data from the day-care centres exist in written form sent to the study headquarters and are later imported electronically. The CATI data are collected and stored electronically. Some of the outcome measures (e.g. care level) are collected in both ways.

Because data collection for the primary outcome variables is conducted at the day-care centres, follow-up data on drop-outs due to death or transfer to a nursing home cannot be collected. If caregivers cannot be reached by telephone for the CATI after three tries, they are sent the questionnaires by mail with the request to mail the questionnaires back.

A pseudonym is created for the electronic data, and it cannot be used for user identification. Only the key file contains information about a person’s identity and pseudonym. All of the data (including written documents, key files, etc.) are kept securely in a locked file, and only the researchers have access to the data.

### Data quality management

All of the groups involved in the study (MAKS therapists, counsellors for the informal caregivers, testers, CATI interviewers, and monitors at the day-care centres) are thoroughly trained for their respective tasks by the study headquarters staff. When they have questions, the members of all groups could contact the study headquarters at any time by phone or in writing.

In order to ensure the validity of the data, the data sources (tests, CATIs, day-care centres) are subjected to a random internal audit. To obtain evidence of the inter-rater reliability of the ETAM test and the CATIs, 5% of the baseline data were collected with the participation of a second person who is there to observe. Four (24%) of the day-care centres in the intervention group will be visited by personnel from the study headquarters during the first 6 months to monitor how the MAKS therapy is conducted (treatment adherence), the quality of the documentation (deviations from the manual and extraordinary events), and the attendance of the study participants.

The quality of the data is guaranteed by strict data monitoring at the study headquarters over the entire period of data collection. In addition, as some of the data are collected in two ways (e.g. care level) at the day-care centre and via a CATI with the caregiver, independent source document verification will be performed. Plausibility checks and logical considerations about the relationships between associated variables will be performed. Regular backups will be carried out and saved on an external hard drive.

### Analysis

#### Data analysis

Only researchers at the study centre in collaboration with the Institute of Health Economics and Health Care Management will assess the results. Our cooperation partner will check the plausibility of the data independently. Thus, there is no need for a data monitoring committee.

The data analyses will be performed with the aid of the “IBM SPSS Statistics 21” software.

If at least 80% of the items on a test have been answered, we will impute missing values from the mean score of the existing items. However, if more than 20% of the items on a test are missing for any given person (e.g. because a participant refuses to complete the test), we will compute the score according to the expectation maximum (EM) algorithm, which uses the variables that explain the greatest proportion of variance in the missing variable.

All changes to the data due to checking for errors, data quality management, or the handling of missing values will be documented.

In order to be able to assess the quality of the randomisation, the baseline data from the intervention and control groups will be examined for statistically significant differences.

The two hypotheses on the efficacy of the interventions in people with cognitive impairment and their caregivers will be tested by computing multiple regression analyses. The transition to institutionalised care as an event will be represented by a Kaplan-Meier curve for the intervention and control groups. The hypothesis on the transition to institutionalised care will be evaluated by Cox regression analysis.

As the primary outcome variables cannot be tested at follow-up in participants who dropped out of the study, the primary data analysis strategy will be “as treated”. The level of statistical significance will be set at *p* = 0.05. Results with an alpha error of less than 10% will be classified as statistical trends.

Subgroups will also be analysed exploratively, sub-divided in accordance with the severity of cognitive impairment and the mean frequency of attendance at the day-care centre per week.

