### Sample size estimation

A power analysis was computed on the basis of the authors’ previous experience with the MAKS study in nursing homes [15, 16, 22]. In contrast to the procedure in the MAKS study in nursing homes, the intervention in the DeTaMAKS project had a lower treatment intensity and a shorter duration, and therefore the effect was expected to be markedly lower. We conservatively set an expected effect size of f^2^ = 0.06 for the primary outcome and alpha error of 0.05 and a statistical power of 0.80 and obtained a total sample size of approximately 270 people attending a day-care centre for at least 6 months. Based on pilot study we assumed fluctuation in day-care centre users of 22% over 6 months. Therefore, we concluded that a total of 346 people should initially be included in the study.

The results of the MAKS study in nursing homes also showed that 69% of eligible candidates were willing to take part in the study. The pilot study showed that 56% of the day-care centre users who were screened fulfilled the required criteria for inclusion. This means that a total pool of 1086 day-care centre users was needed to achieve the required sample size. If we assumed approximately 33 users per week, we needed to recruit at least 32 day-care centres.

These day-care centres were large enough to have the space and staff required to carry out the project in accordance with the prescribed conditions.

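### Tests with more than 20% of items missing get one EM-predicted score that is analysed as observed: the standard error is too small if arm is an EM predictor, and the effect is shrunk if it is not

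*Protocol article*

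**What the plan says.** The protocol article (Data analysis) sets two rules for incomplete tests.

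- Few items missing: "If at least 80% of the items on a test have been answered, we will impute missing values from the mean score of the existing" ones. This rule is not at issue here.
- Many items missing: the second rule starts "if more than 20% of the items on a test are missing for any given person", with a participant's refusal as the example. The instruction is then: "we will compute the score according to the expectation maximum (EM) algorithm, which uses the variables that explain the greatest proportion of variance".

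The efficacy hypotheses for users and caregivers "will be tested by computing multiple regression analyses". For the filled scores the article mentions no repeated imputation, residual draw, variance correction or sensitivity analysis. Arm and centre are neither required nor excluded as EM predictors.

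People who have left the study come under a separate sentence: "As the primary outcome variables cannot be tested at follow-up in participants who dropped out of the study, the primary data analysis strategy will be" an as-treated one.

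**The concern.** An EM prediction is a conditional mean. It lies exactly on the fitted surface and has no residual scatter. If it is counted as a measured score, the regression credits the trial with information it does not have.

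The way predictors are chosen adds a second risk. Selection by explained variance favours strong prognostic variables such as the baseline score, and nothing obliges the analyst to keep arm. A prediction made without arm gives treated and control users with the same covariates the same value, which draws the arms together.

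The rule can reach the primary outcomes. On the six-item ETAM, one missing item leaves 5/6 = 83% answered (person-mean rule), but two leave 4/6 = 67% (EM rule). If caregiver questionnaires count as tests, two missing items on the WHO-5 (3/5 = 60% answered) or three on the BSFC-s (7/10 = 70%) also trigger EM. At stake is the validity of either the test or the estimate and its interval, depending on the predictor set.

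**Working it through.** **Inputs from the protocol article.** Sample size estimation gives "expected effect size of f^2^ = 0.06 for the primary outcome and alpha error of 0.05 and a statistical power of 0.80", about 270 analysable users and 22% fluctuation. The inclusion target reproduces: 270 / (1 − 0.22) = 346.2, stated as 346. Data analysis states "The level of statistical significance will be set at" 0.05 without giving sidedness; two-sided is assumed.

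**Inputs assumed, because the article does not give them.** Equal arms; baseline–follow-up correlation 0.7; a share m of 6-month scores filled, from 2% to 20%; filled users have no answered items; missing completely at random; no clustering.

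**Effect size.** With equal arms and all of f² due to arm, f² = d²/4, so d = 2√0.06 = 0.49 residual SD. Arm then explains at most 0.06/1.06 = 5.7% of variance, whereas a baseline correlation of 0.7 explains 0.7² = 49%. A rule that picks the strongest predictors can therefore pass arm over.

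**Case A: arm among the EM predictors.** Filled scores leave the coefficients unchanged and have zero residuals.
- The residual variance is divided by about n instead of (1 − m)n, a factor √(1 − m) on the standard error.
- The design information is counted for n people instead of (1 − m)n, another √(1 − m).
- Together: reported SE ≈ (1 − m) × true SE, so type I error ≈ 2[1 − Φ(1.96(1 − m))].
- At m = 5%, 10% and 20% the critical value becomes 1.86, 1.76 and 1.57, giving 6.3%, 7.8% and 11.7%.

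**Case B: arm not among the predictors.** The estimate is multiplied by about (1 − m): 0.49 × 0.95 = 0.47, × 0.90 = 0.44, × 0.80 = 0.39. The reported SE shrinks by the same factor, so the test statistic is close to that of a complete-case analysis and type I error stays near 5%. The damage is to the estimate and its interval.

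**Simulation** (6,000 trials per setting; fill-in by regression prediction, then ordinary regression on arm and baseline; SE and estimates in residual SD; coverage at a true effect of 0.49):

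| m | A: reported / true SE | A: type I error | A: coverage | B: mean estimate | B: type I error | B: coverage |
|---|---|---|---|---|---|---|
| 2% | 0.121 / 0.123 | 5.6% | 94.7% | 0.482 | 5.1% | 94.9% |
| 5% | 0.119 / 0.126 | 6.0% | 93.7% | 0.462 | 4.6% | 94.4% |
| 10% | 0.116 / 0.127 | 7.3% | 92.7% | 0.443 | 4.9% | 93.2% |
| 20% | 0.109 / 0.138 | 12.1% | 87.8% | 0.393 | 5.1% | 85.6% |

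Other runs of the same set-up gave type I error in case A of about 6–8% at 5–10% filled and 11.5–12.1% at 20%. Complete-case analysis of the same data was unbiased, with type I error near 5% and coverage near 95%.

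**Answered items used in the prediction.** With one partial score added as a predictor (assumed noise 0.45 SD), type I error in case A fell to 5.3%, 5.9% and about 6.3–6.5% at 5%, 10% and 20% filled. In case B the 0.49 effect was estimated as 0.48, 0.48 and 0.46.

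**The case against.** Four objections deserve an answer.

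- **The figures are close to a worst case.** They assume total refusal and prediction from baseline alone or with arm. Refusal is only the article's example, and a user with two missing ETAM items still has four answered ones. This stands, which is why the smaller figures are shown beside the larger.
- **No refusal rate is documented.** A reader might infer from the 19–35 minute ETAM and a dementia population that refusal will be common. The documents do not support that. The 22% fluctuation concerns people leaving the centres. Severe dementia and inability to communicate are excluded, and participants had already undergone cognitive testing at screening. Two of the four primary outcomes are short caregiver questionnaires taken by telephone with postal back-up, to which the argument about a long performance test does not apply.
- **Detail may sit in an analysis plan that is not shown.** Such a plan could name the predictors. That would settle which harm applies, but would not remove both: a single conditional-mean fill-in followed by ordinary regression is a stated rule. The promise to document all data changes does not correct a standard error.
- **Treating refusers and drop-outs differently is not itself the fault.** A reader might want one rule for both. The article gives a reason for the separation (drop-outs cannot be tested), and drop-outs include deaths, after which an ETAM or MMSE score has no meaning. The as-treated strategy is a separate issue.

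**Conclusion.** The point holds in a limited form. The stated rule gives a wrong standard error (arm in the EM model) or a wrong estimate with a misleadingly narrow interval (arm out).

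A reader might infer that the plan both inflates type I error and shrinks the effect. The calculation does not support this: the two are alternatives, and with arm left out type I error stays near 5%. Nor is 12% an expected error rate. It needs 20% of analysed scores, 54 of 270, to be filled with no answered items and with arm in the model.

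Under total refusal the harm is trivial at about 2% filled, modest at 5–10% and material at 20%, and much smaller where answered items inform the prediction. These sizes rest on an assumed correlation of 0.7, data missing completely at random and no clustering. If the more impaired refuse more often, further bias could arise that is not modelled here. Because the filled share, the predictors and the amount of partial data are all unknown, the size, and which of the two harms applies, cannot be fixed from the documents.

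**What to change.** Replace the single EM fill-in of total scores with one of the following:

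- multiple imputation, with at least 20 sets combined by Rubin's rules, in a model that always includes arm, centre, region, baseline score and any answered items; or
- a likelihood-based model of the observed baseline and 6-month scores, which needs no fill-in under missing at random. The article currently plans only multiple regression, so this model would have to be specified.

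Whichever is chosen, report a sensitivity analysis without filled scores, and do not impute scores after death.

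The cost is analysis wording, slightly more programming and slightly wider intervals. No new data are needed.
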